## Abstract

**Background:**

American Indian adolescents have one of the highest rates of teen pregnancy and repeat teen births in the US. Substance use is a significant risk factor for unprotected sex, and American Indian adolescents have the highest substance use-related morbidity and mortality of any US racial group. Despite these disparities, there are no existing, evidence-based programs for pregnancy prevention that have been rigorously evaluated among American Indian teens.

**Methods:**

The proposed study is a randomized controlled trial to test the efficacy of a comprehensive sexual and reproductive health program developed in partnership with an American Indian community. Participants will be American Indians ages 11–19 and their parent or trusted adult, randomized to receive the control condition or intervention called Respecting the Circle of Life: Mind, Body and Spirit. The intervention includes eight lessons delivered to self-selected peer groups during a summer basketball camp and one lesson delivered to the youth and parent/trusted adult together within 3 months after camp. All lessons are administered by trained community health workers from the participating American Indian community. Youth and parent/trusted adult participants will complete assessments at baseline, 3, 9, 12, 24 and 36 months post-intervention completion. The primary outcome variables are sexual/reproductive health knowledge, sexual initiation, condom use self-efficacy and intent to use a condom at next sex as changed from baseline to post-intervention between intervention and control participants. Selected primary outcomes are applicable to all study participants.

**Discussion:**

Currently there are no sexual and reproductive health programs designed specifically for American Indian youth that have been rigorously evaluated and found to have an evidence base. Respecting the Circle of Life is highly innovative by incorporating lesson delivery into a summer basketball camp and involving parents or other trusted adults in curriculum administration. If found successful, it will be the first evidence-based program for teen pregnancy prevention for American Indian youth and adolescents.

**Trial Registration:**

Clinicaltrials.gov, NCT02904629. Retrospectively registered on 23 September 2016.

**Electronic supplementary material:**

The online version of this article (doi:10.1186/s13063-017-1842-6) contains supplementary material, which is available to authorized users.

## Background

American Indian (AI) adolescents have one of the highest rates of teen pregnancy of all US racial groups [1]. In 2013, American Indian/Alaska Native (AI/AN) females 15 to 19 years old had the third highest teen birth rate in the US (31 per 1000 compared with 27 per 1000 nationally), and in 2010, they had the highest prevalence of repeat teen births (21.6% compared with 20.9%, 20.4% and 14.8% among Hispanic, Black and White females, respectively) [1–3]. Nearly half (41%) of AI females begin childbearing in adolescence and within their lifetime bear twice as many children as the general US population [2, 3]. Compared with US All Races, AI adolescents are more likely to have ever had sex (69% vs. 47%), had sex for the first time before age 13 (11% vs. 6%), had sex with four or more persons during their lifetime (22% vs. 15%) and drank alcohol or used drugs prior to sex (32% vs. 22%) [4–6].

Substance use is one of the most significant risk factors for unprotected sex, and AI teens have the highest drug-related morbidity and mortality of any US racial group [7–10]. Compared to all other US adolescents, in 2009, AI youth were more likely to engage in past-month binge drinking (30% vs. 24%), marijuana use (32% vs. 21%) and cocaine use (6% vs. 3%), and nearly three times as many reported lifetime methamphetamine use (11% vs. 4%) [11].

Therefore, one tribal community in partnership with long-term academic research collaborators developed a comprehensive sexual and reproductive health program for AI adolescents. In the participating tribal community, unintended and teen pregnancies are high and many children are born to unwed mothers. These challenges are perpetuated by the absence of sexual and reproductive health education in the local school curriculum and the lack of evidence-based teen pregnancy prevention programs targeting AI adolescents.

“Respecting the Circle of Life: Mind, Body and Spirit” was adapted in 2010 by the tribal-academic partners from an evidence-based intervention (EBI) for the prevention of HIV/AIDS called “Focus on Youth (FOY) + Informed Parents and Children Together (ImPACT).” FOY consists of eight lessons delivered weekly by pairs of adult interventionists from the community to self-selected same-sex peer-groups in community centers [12]. ImPACT is a separate, one-time lesson delivered to the teen and parent together by an adult interventionist after the initial eight lessons; it is comprised of a DVD and workbook. FOY + ImPACT first targeted low-income, urban African-American youth and has a track-record of successful cross-cultural replication in various international contexts [13–16].

FOY + ImPACT was selected for adaptation by tribal-academic partners because of its targeted age group (adolescents), skills-focused curricula, theoretical underpinnings promoting positive protective factors and capacity for delivery by trained community members. Further, FOY + ImPACT’s core elements and key characteristics matched community-identified needs for this program including: (1) a lack of sexual health education in schools; (2) the role of substance use as a primary risk factor for early sexual and substance use initiation and unprotected sex; (3) multi-level curriculum administration including through peer groups and with parents or other trusted adults.

To adapt FOY + ImPACT, tribal-academic partners utilized a community-based participatory research approach, which included leadership from a Community Advisory Board (CAB), continuous engagement with tribal stakeholders and qualitative research comprising 18 focus groups with teens and parents from the participating tribal community. Key themes emerged from the qualitative data collection namely limited knowledge of and use of sexual risk reduction strategies, low condom use self-efficacy, poor negotiation and communication skills between adolescent sexual partners, the influence of peers on sexual decision-making (especially among males) and infrequent parent-child communication related to sexual health in families [17].

Reflecting on these themes, we made the following adaptations to the FOY + ImPACT curriculum: (1) enhance content around reproductive anatomy, sexual and reproductive health information, pregnancy prevention strategies and applied skills training; (2) teach proper condom and contraceptive use and community- and youth-centered strategies for overcoming access barriers; (3) build in comprehensive substance use prevention components teaching peer refusal and pro-peer relations; (4) reflect the importance of social pressure on males and self-esteem and connectedness on females for sexual decision making [17]; (5) modify all content to reflect the local language, include familiar characters, and add culturally relevant examples and scenarios; (6) reproduce the ImPACT DVD with local actors and testimonials, include traditional Native storytelling, and add emphasis on the balance among physical, spiritual and emotional health.

Several changes were also made to curriculum delivery structure [18]. Qualitative findings indicated the FOY peer-group component should be collapsed from 8 weekly to 8 daily sessions and implemented during a summer basketball camp [17]. Additionally, offering the ImPACT youth-parent lesson to “non-traditional” parents and/or caregivers that play an important role in youths’ lives was determined appropriate and necessary. The original architect of FOY + ImPACT, [name], endorsed all changes and adaptations as feasible and highly practical.

In 2011 and 2012, we conducted a pilot trial of the Respecting the Circle of Life (RCL) peer-group component (8 lessons taught during summer basketball camp) without the additional youth-parent lesson [18, 19]. Immediately post-camp, RCL participants had significantly greater condom use self-efficacy, intention to use condoms at next sex, HIV/STI prevention and transmission knowledge, partner negotiation skills related to alcohol and drug use during sex, and belief in the protective effects of condoms and abstinence [19]. RCL participants were also more likely to talk with a family member or other adult about HIV/AIDS [19]. Regarding the theoretical constructs underpinning the RCL intervention, all positive protective factors, including self-efficacy (ability to engage in behaviors to reduce risk for STIs/HIV), response efficacy (ability of the protective behavior to actually reduce risk, i.e., efficacy of condoms to prevent infection and pregnancy) and response cost (negative impacts of engaging in the protective behavior), were significantly improved among RCL participants [19].

Improvements in condom use self-efficacy, HIV/STI prevention and transmission knowledge, belief in the protective effects of condoms, talking with a family member or other adult about HIV/AIDS, and response efficacy were sustained at 6 months follow-up [19]. Changes in condom use self-efficacy and response efficacy were sustained through 12 months [19]. All other impacts attenuated at 12 months, which is consistent with previous trials of the FOY peer-group component [14–16, 20]. In an effort to extend intervention impacts past 6 months, previous research groups added the ImPACT youth-parent component and found both existing and additional intervention impacts (including substance use initiation and subsequent substance use) sustained through 24 months [21, 22].

Thus, the aim of this trial is to evaluate the effect of the RCL intervention, including both peer-group (8 lessons) and youth-parent components (1 lesson), on knowledge, attitudes and behaviors associated with unprotected sex and unintended pregnancy among an exclusive sample of AI adolescents. Utilizing a randomized controlled trial (RCT) design, we will test whether the RCL intervention affects well-established intermediate outcomes and risky sexual behaviors that predict a long-term impact on the incidence of teen pregnancy [23].

## Methods/Design

### Trial Design

The study is a randomized controlled superiority trial with two parallel groups and primary endpoints of condom use self-efficacy, condom use intention, sexual and reproductive health knowledge, and delayed sexual initiation 9 months post-intervention. Block randomization will be performed with a 1:1 allocation.

### Participants

Youth participants will be of AI ethnicity, ages 11 to 19 and have primary residence on or near the participating tribal reservation community. Parent/trusted adult participants will be chosen by the youth and be the parent/legal guardian of the participating youth or another family member or trusted adult over the age of 18. If the youth choses an adult who is not the legal guardian, the adult must be approved by the legal guardian. Participants who are unable to fully participate in the evaluation assessments or intervention components will be excluded (see Table 1 for Inclusion and Exclusion criteria). All participants will complete informed consent to participate; youth under age 18 will have parent/guardian consent.

**Table 1 Tab1:** Inclusion and exclusion criteria

Inclusion criteria		
	Youth	-Self-identified American Indian -11-19 years old -Primary residence on or near the reservation -Written informed consent (parent/guardian consent if 11–17 years old)
	Parent/trusted adult	-Parent, legal guardian or trusted adult -18 years old or older -Primary residence on or near the reservation -Written informed consent
Exclusion criteria		
	Youth	-Unwilling to be randomized -Unable to complete intervention because of cognitive limitations -Unable to complete evaluation (i.e., planned move, residential treatment, etc.)
	Parent/trusted adult	-Unwilling to be randomized -Unable to complete intervention because of cognitive limitations -Unable to complete evaluation (i.e., planned move, residential treatment, etc.)

We will use non-probability sampling to recruit participants through public postings in community gathering spots (i.e., supermarket, daycares, fitness center, etc.), through public service announcements on the local radio, by print advertising in the local newspaper, during public gatherings (i.e., health fairs, parades, etc.) and through local schools. We will recruit three cohorts of participants and host three summer basketball camps (2016, 2017 and 2018).

### Intervention: Respecting the Circle of Life: Mind, Body and Spirit (RCL)

RCL consists of a peer-group (adapted FOY lessons) and a youth-parent component (adapted ImPACT lesson). The peer-group component consists of eight lessons, each lasting ~120 min, delivered by two trained AI community health workers to self-selected same-sex peer groups of 8–12 AI youth. The eight lessons are delivered once per day during the 8-day summer basketball camp. The youth-parent component is one educational lesson lasting 90–120 min delivered within 3 months after the end of camp, to the youth and parent/trusted adult, together with an AI community health worker.

RCL focuses on: (1) extrinsic rewards, by teaching decision-making related to communication and negotiation skills around sex, as well as information regarding birth control and condom use, and (2) intrinsic rewards, by emphasizing values clarification and goal setting. Peer-group instruction incorporates discussion, lectures, games, role playing and storytelling. RCL content covers: (1) reproductive and sexual health education; (2) instruction about condom use, contraception, STIs, safe sex practices and pregnancy prevention; (3) partner communication and negotiation skills for sex and substance use; (4) peer refusal for unwanted sex and substance use; (5) peer norms related to delaying sexual initiation; and (6) linkages to community resources. Youth-parent instruction incorporates a DVD and skills-based activities focused on: (1) information about sexual and reproductive health; (2) promoting family values pertaining to sex and substance use; (2) techniques for youth-parent communication and effective parental monitoring; (3) how to support youth condom and contraceptive use; and﻿ (4) decision-making pertaining to sex.

### Control Program

The control program is identical in structure and delivery mode to RCL and consists of peer-group and youth-parent components. The control program does not include any content pertaining to sexual and reproductive health, to ensure no overlap. Lesson content includes: (1) knowledge about food labels and general nutrition; (2) information about different types of physical activity; (3) activities to encourage youth to eat healthy; and (4) relaxation techniques. Implementing a control program identical in structure but different in content will ensure observed impacts on key outcomes can be attributed to the content of the RCL program.

### Randomization

Participants will be individually randomized to receive the intervention or control program. Participants will be assigned to either program through a stratified block randomization sequence using Stata 14 [24] to ensure a 1:1 allocation of study conditions occurs within each gender and age sub-group (11–12, 13–15 and 16–19). Since both the RCL and control program include a youth-parent component, siblings will be randomized to the same group.

### Data Collection Time Points

The flow of participants from recruitment through the end of the study is illustrated in the SPIRIT Study Figure (Fig. 1). Youth and parent participants will be assessed at three time points: baseline, 3 months and 9 months post-intervention completion. Due to the nature of the intervention, neither participants not interventionists can be blinded to group allocation. Therefore, all follow-up assessments are done by ﻿research staff (independent evaluators) that are blinded. If unblinding occurs, another independent evaluator will be brought in to re-establish blindness. Youth and parent participants will be given a gift card after completing each assessment totaling $100 for youth and $60 for parents, respectively.

**Fig. 1 Fig1:**
[figure not shown]
SPIRIT Figure

All data collection will be administered via ACASI (Audio Computer Assisted Self-Interview) technology on a laptop or tablet, which includes an audio component for participants with literacy challenges. This method has been shown to decrease response bias in AI communities, especially around sensitive topics [25]. The youth baseline assessment will be administered during two pre-camp registration days prior to randomization; the parent-trusted adult baseline will be administered prior to camp at the time of consent. All youth and parent/trusted adult follow-up assessments will be delivered in participant’s homes, at school or another location of their choosing.

### Outcomes

Youth participants will complete the Youth Health Risk Behavioral Inventory (YHRBI) developed by Stanton and colleagues to evaluate the FOY + ImPACT program [26]. The YHRBI assesses demographics; knowledge, intentions and past experience regarding risk and protective behaviors; sexual perceptions; and behaviors including sexual initiation, alcohol/drug use during sex, condom use and contraceptive use. The reliability of this assessment has been established in previous evaluations [26], including our pilot trial in which the majority of sub-scales had Cronbach’s alpha values ≥0.70 [18].

Youth and parent/trusted adult participants will also complete the Parental Monitoring Scale and Parent Adolescent Communication Scale, both successfully used in previous trials of FOY + ImPACT [27, 28]. The Parental Monitoring Scale assesses perceptions of parental supervision, and the Parent Adolescent Communication Scale measures family-based communication. During the formative work previously discussed, we adapted all three scales with the participating tribal community to ensure use of local terminology, age and culturally appropriate examples, relevant theoretical constructs, clarity and flow.?>

#### Primary Outcome Measures

The primary outcome variables are sexual/reproductive health knowledge, sexual initiation, condom use self-efficacy and intent to use a condom at next sex as changed from baseline to post-intervention between intervention and control participants. These variables were chosen because they are applicable to all study participants.

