#### Secondary Outcome Measures

Secondary outcome variables will be examined among sexually active participants including condom use at last sex, number of sexual partners, sex without a condom in the last 3 months and sex without contraception in the last 3 months. It is expected that 20-25% of study participants will be sexually active. The impact evaluation will also have exploratory outcome variables including parental engagement (communication and monitoring), youth substance use and substance use just prior to and/or during sex.

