### Sample Size Calculation and Statistical Analysis

Our goal is to recruit 567 youth (and their parent/trusted adult) balanced within two age groups (11–12, 13–15 and 16–19), for a total of 1134 participants (567 youth and 567 parents/trusted adults). We expect a maximum attrition rate of 25%, based on past rates in similar evaluations [18, 19, 29, 30].

Sample size estimates were based on the variables of condom use self-efficacy and sexual initiation because these confirmatory research questions apply to all study participants, and prior studies have shown them to be associated with reductions in risky sexual behavior, teen pregnancy and STI incidence [23]. We hypothesize that the RCL intervention will increase condom use self-efficacy in the intervention group compared to the control group and that the intervention group will have a lower proportion of participants who initiate sex, compared to controls, at study end line.

The condom use self-efficacy scale ranges from 1–5. Our pilot trial [18] provided data on the condom use self-efficacy score among the control group (mean = 2.6, SD = 1.0), degree of intra-team correlation (“k” = 0.12) and potential loss to follow-up over 9 months (20% average reduction in team size, i.e., from 9 down to 7.2 youths). Although this trial will utilize individual randomization, the intervention will be carried out with teams of 8–12 participants each, which will require accounting for intra-team correlation.

We will use the average of two follow-up measures of condom use self-efficacy per participant (intra-measure correlation = 0.7) to reduce error in outcome measurement [31]. To achieve 90% power to detect a theoretically meaningful between-group difference of 0.47 points on this scale over 9 months post-intervention, ~32 teams per study arm will be required. Thus, we will enroll and randomize a total of *n* = 284 participants per study arm (32 teams/arm *9 participants/team), for a total sample size of *n* = 567 participants. We have reduced the significance level used in sample size calculations to 0.0125 to account for multiplicity corrections during analyses. This same sample size will be sufficient to detect a 19.7% between-group difference, with 80% power and 0.0125 significance level, in the percent of participants who report ever having had sex. This estimate is conservative based on our past retention rates and accounts for up to 25% loss to follow-up, while adjusting for the intra-team correlation.

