This sample size will also be able to detect meaningful differences between the intervention and control groups with at least 80% power, given the assumptions listed above: 6.7% between-group difference in reproductive/sexual health knowledge score [estimating a mean score (SD) of 76% (16%) in the control group] and 20.5% between-group difference in intention to use a condom at next sex (estimating 55% in the control group).

Study hypotheses will be initially tested under an “intent-to-treat” model in which data are analyzed according to randomization assignment. We will then conduct “completer analyses” on those subjects finishing at least two-thirds of the 9 intervention sessions. Intervention impact will be evaluated by comparing primary study outcomes between intervention and control groups across the three time points: baseline, 3 and 9 months post-intervention. Initially, summary scores of outcomes will be stratified by participation in the intervention versus control groups and by time point and compared using chi-square tests (for binary or categorical outcomes), t-tests and analysis of variance (for continuous outcomes). The equivalence of the two study groups at baseline will be compared across a range of background variables. Generalized linear mixed effects models (GLMMs) accounting for within-group correlation across longitudinal data will then be applied.

Outcomes will be modeled as a function of group assignment and time since intervention. The association between outcomes and time will be explored visually using scatterplots and lowess smoothers. Restricted cubic splines will be added to reflect deviations from linearity. GLMM with random intercepts for peer group and study participant will be used to account for the hierarchical structure of the data: peer group, participants nested within peer group and assessments nested within study participants. If siblings enter the study together during the same wave, they will be randomized to the same study group (intervention or control) to limit contamination. In this case, analyses will be adjusted to take into account intra-sibling correlation as well. Missing data will be handled as follows: (1) document reason(s) for missing data to inform model development; (2) assess treatment dropouts to do intent-to-treat analysis; (3) conduct sensitivity analysis to compare inferences that are based on different plausible reasons for missingness [32, 33].

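### Sexual initiation is a primary outcome said to apply to all youth and is powered as ever having had sex, but youth already experienced at baseline cannot initiate, and the planned participant-level random-intercept model does not suit the outcome

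*Protocol article*

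**What the plan says.** The outcome is described in several ways in the protocol article.

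- Trial Design lists the endpoint as "delayed sexual initiation 9 months post-intervention".
- Primary Outcome Measures names sexual initiation, takes all primary outcomes "as changed from baseline to post-intervention between intervention and control participants", and justifies the choice: "These variables were chosen because they are applicable to all study participants".
- Sample Size Calculation and Statistical Analysis repeats that the question applies to everyone. Its hypothesis is that "the intervention group will have a lower proportion of participants who initiate sex, compared to controls, at study end line", but its power statement is to "detect a 19.7% between-group difference, with 80% power and 0.0125 significance level", measured "in the percent of participants who report ever having had sex". No control proportion is given.

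The Participants section and its Table 1 set no criterion on sexual experience. Secondary Outcome Measures states: "It is expected that 20-25% of study participants will be sexually active". It does not say whether this is a baseline or a lifetime figure.

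For the primary outcomes, compared across baseline, 3 and 9 months, the analysis is: "GLMM with random intercepts for peer group and study participant will be used to account for the hierarchical structure of the data".

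**The concern.** Initiation is an event that can happen only to someone who has not yet had sex. Ever having had sex is a prevalence that includes everyone who started before the trial. The Trial Design wording and the hypothesis point to the first. The only numerical specification uses the second, over all youth. A participant who answers yes at baseline answers yes at 9 months whatever the programme does, so the stated reason for choosing this outcome is false for that participant.

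Two things are at stake on a confirmatory endpoint. The arm difference is diluted and carries noise from youth who cannot respond. And a model built for responses that can go up and down is applied to a state that, once entered, is not left.

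**Working it through.** **Inputs from the protocol article:** 567 youth allocated 1:1, teams of 9, so 567 / (2 × 9) = 31.5 teams per arm (the text rounds to about 32); intra-team correlation 0.12; loss up to 25%, so team size 9 × 0.75 = 6.75; significance level 0.0125, taken as two-sided (z = 2.498).

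**Assumptions, not in the article:** share b experienced at baseline 20–35%; 9-month control incidence among the rest 10–20%; the programme halves it. The 20–25% sexually active figure is borrowed as a guide to b. The 0.12 was estimated for condom self-efficacy and is carried over.

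**1. The plan's own figures.** Design effect 1 + 5.75 × 0.12 = 1.69. With 32 teams, effective n per arm = 32 × 6.75 / 1.69 = 127.8. This reproduces the knowledge figure: (2.498 + 0.842) × 16 × √(2/127.8) = 6.68, against the stated 6.7. The 19.7 points cannot be reproduced outright without a control rate. On the same effective n it fits a control rate of about 44% or 76% with a pooled null variance, and about 46.5% or 73% with an unpooled one.

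**2. Dilution.** Difference in all youth = (1 − b) × difference in inexperienced youth. For 19.7 points overall:

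- b = 20%: 19.7 / 0.80 = 24.6 points among the inexperienced
- b = 25%: 19.7 / 0.75 = 26.3 points

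At least that share of inexperienced controls must start having sex by 9 months for the difference to be possible.

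**3. Power at b = 25%, incidence 15% v 7.5%.** Unpooled normal approximation with 31.5 teams. Effective n in all youth = 212.6 / 1.69 = 125.8. Among the inexperienced: n = 159.5, team size 5.06, design effect 1.49, effective n 107.2.

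| Comparison | Proportions | Standard error | Difference / SE | Power |
|---|---|---|---|---|
| Ever had sex at 9 months, all youth | 36.25% v 30.63% | 0.0594 | 0.95 | 6% |
| Change from baseline, all youth | 11.25% v 5.63% | 0.0349 | 1.61 | 19% |
| First sex, baseline-inexperienced | 15% v 7.5% | 0.0429 | 1.75 | 23% |

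In the second row experienced youth contribute zero change, assuming consistent answers. If the programme prevented every initiation, the three powers would be 29%, 93% and 97%.

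Over b = 20–35% and incidence 10–20%, halved, restricting to inexperienced youth multiplies power by 2.7 to 4.8 relative to raw prevalence (both tails counted), but only by 1.14 to 1.34 relative to change from baseline.

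**4. What restriction can detect.** With 32 teams and b of 20–25%, effective n is about 113 to 109 per arm. At 80% power the detectable drop is 9.7–9.9 points from 10% control initiation, 14.7–14.9 from 20% and 18.0–18.3 from 30%. A halving from 20% has 33–35% power, and from 30% has 56–58%.

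**5. The mixed model.** With consistent reporting over three visits only the patterns 000, 001, 011 and 111 occur. A logistic model with a participant random intercept and separate arm-by-visit means was fitted to expected counts: 213 per arm, 22.5% experienced, cumulative incidence 5% and 15% in control and half that under the programme.

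| Random-intercept SD | Minus log-likelihood | Arm-by-time log odds ratio, 9 months |
|---|---|---|
| 1 | 607.4 | −0.34 |
| 5 | 406.7 | −1.0 |
| 20 | 367.8 | −3.11 |
| 80 | 364.55 | −13.06 |

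The saturated value is 364.52. The fit keeps improving as the SD grows, because in the limit each participant has a single latent threshold, which reproduces absorbing patterns exactly. The coefficient merely scales with the SD (−3.11/20 = −0.156; −13.06/80 = −0.163), so the odds ratio has no stable value.

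**The case against.** Four counter-arguments deserve weight.

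- **Randomisation protects the contrast.** Youth complete baseline before randomisation, which is stratified by gender and age group. Ever having had sex at 9 months, compared by arm, is a valid intention-to-treat contrast, and the planned chi-square test on it is usable. This stands. A reader might infer that the endpoint is biased; the article does not support that. The loss is in power and in matching the stated question.
- **The outcome is taken as change from baseline.** Primary Outcome Measures says so and the longitudinal comparison includes baseline. On that reading fixed yes answers add little noise and the power gap is 19% v 23%. This stands too. A several-fold gain from restriction is therefore tempting to claim but holds only against unadjusted 9-month prevalence.
- **Low incidence matters more than the denominator.** After restriction the main scenario still has only 23% power. This also stands.
- **Coding and model form may be left to an analysis plan.** This stands in part. Ever having had sex appears only in the power sentence, and the model sentence is generic to all outcomes. But the article affirmatively says initiation applies to everyone and names the participant random intercept, and neither is right for this outcome. Recanted answers would give a finite participant variance, though not an interpretable one.

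**Conclusion.** The concern holds in a limited form. The claim that sexual initiation applies to all participants is wrong for youth who are experienced at baseline. The article's wordings mix incidence with prevalence, and the only quantified version is prevalence in all youth.

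The size depends on which analysis is meant: a large loss of power if 9-month prevalence is compared without baseline, and a small one if change from baseline is used. The required 24.6 to 26.3 points among inexperienced youth rests on b being 20–25%. The power figures rest on assumed incidence, an assumed halving, and a correlation borrowed from another outcome.

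The model criticism does not depend on those rates. With consistent reporting, the random-intercept variance has no finite maximum-likelihood estimate.

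A reader might also infer that 19.7 points is arithmetically impossible, since 44% less 19.7 points is 24.3%, below a 25% experienced share. That does not follow: the control rate is not given, the implied rate shifts with the variance formula (46.5% less 19.7 is 26.8%), and b is not stated.

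**What to change.** 1. Reconcile Trial Design, Primary Outcome Measures and the sample-size section on one definition: first report of sex by the 9-month assessment among youth who report at baseline that they have never had sex. The subset is fixed before randomisation, so the comparison stays randomised.
2. Analyse it once per participant, or in discrete time over the two follow-ups, using a logistic or complementary log-log model with arm, age group, gender and a team random intercept, and no participant random intercept.
3. Report ever having had sex in all youth descriptively.
4. Correct the statement that the primary outcomes apply to all participants.
5. Restate the detectable difference for this subset together with its assumed control rate.

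The cost is wording and a filter: the baseline questionnaire already covers sexual initiation. The endpoint would use fewer participants (about 75–80% if the 20–25% is a baseline figure of sexual experience), and modest effects remain underpowered, which the restated calculation should say openly.
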